**Methods:**

We will collect vertebral and peripheral blood from 500 elderly OVCF patients undergoing surgery, extract DNA, and generate whole genome genotype data and DNA methylation data. Observation indicators will be collected and combined with one-year follow-up data. A healthy control group will be selected from a natural population cohort. Epigenome-wide association studies (EWAS) of osteoporosis and bone mineral density will be conducted. Differential methylation analysis will compare candidate gene methylation patterns in patients with and without refracture. Multi-omics prediction models using genetic variants and DNA methylation sites will be built to predict OVCF risk.

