### Sample size

The power of EWAS is essential for detecting differentially methylated positions (DMPs) between cases and controls. Similar to GWAS, the power of EWAS depends on four key factors, including study design, sample size, effect size, and burdon of multiple test correction. Previous simulation analysis has shown that a sample of 500 cases and 500 controls would achieve 80% power to detect differential methylation at epigenome-wide significance (*P* < 1E-6) with a methylation odds ratio of 1.28 or mean methylation differences of 5% in case–control designs of EWAS (cite the original pubication) [19]. Therefore, we aim to recruit 500 elderly patients with OVCF who underwent vertebral augmentation surgery, as well as 500 healthy controls matched for age, gender, and race from the CAS cohort who did not develop OVCF or osteoporosis. This sample size will provide adequate statistical power for detecting significant differences in DNA methylation levels between cases and controls and enable us to identify epigenetic markers associated with refracture after vertebral augmentation surgery for OVCF.

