### Biomarker identification and prediction analysis

The GWAS of bone mineral density will be carried out in PLINK using linear regression model, assuming an additive allele effect. Covariates for age, gender, drug usage and the first five principal components to account for residual population structure will be also included in the model. The genomic control inflation factor will be used to adjust the *p*-values. The adjusted *p*-values equal to or smaller than 5E − 8 will be considered as genoome-wide significant. We will conduct a GWAS using case–control design to invesgate the genetic variants associated with osteoporosis.

This study will use whole-genome methylation data from vertebral and peripheral blood samples of 500 osteoporosis patients with recurrent fractures after vertebral augmentation and 1000 natural population controls from the Chinese Academy of Sciences. To identify differentially methylated positions (DMPs) between patients with and with out refracture, we will perform an epigenome-wide association study (EWAS) and meQTL analysis. Patients with refracture who underwent vertebral augmentation will be selected as cases, and an equal number of patients without refracture will be selected as controls based on age range and epidemiological indicators such as BMI, disease, and medication history. We will analyze changes in methylation levels of osteoporosis- and bone mineral density-related sites in elderly patients with refracture within one year after surgery. The R language DMRfinder package will be used for analysis, and functional annotation of the identified DMPs and differentially methylated regions (DMRs) will be performed.

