To predict BMD and OVCF risk, we will use multiple linear regression and multiple logistic regression models, respectively. We will include sex and age as predictors along with independent BMD-related genetic variants identified in previous studies and methylation sites identified in this study. Fracture risk score will also be evaluated based on age, gender, bone mineral density (BMD), previous fracture history, family history, and other risk factors. Prediction accuracy will be estimated using the R-squared correlation (R2) for BMD and the area under the curve (AUC) for OVCF risk. Sensitivities and specificities will be calculated using confusion matrices, where the predicted probability greater than a certain threshold (t) will be considered the predicted shape type, and t will be optimized to maximize the sum of sensitivity and specificity.

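### The prediction analysis does not separate discovery and tuning from evaluation, so its accuracy figures are optimistic as written, by an amount that the unstated site-selection rule decides

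*Protocol article*

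**What the plan says.** The Methods part of the abstract announces the aim: "Multi-omics prediction models using genetic variants and DNA methylation sites will be built to predict OVCF risk". The section Biomarker identification and prediction analysis gives the steps.

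- **Models.** For BMD and OVCF risk, "we will use multiple linear regression and multiple logistic regression models, respectively". No penalisation is named.
- **Predictors.** Sex and age, together with "independent BMD-related genetic variants identified in previous studies and methylation sites identified in this study".
- **Accuracy.** "Prediction accuracy will be estimated using the R-squared correlation (R2) for BMD and the area under the curve (AUC) for OVCF risk".
- **Cut-off.** Sensitivity and specificity come from confusion matrices at a threshold t, and "t will be optimized to maximize the sum of sensitivity and specificity".

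The section does not say which participants are used at each step, or what rule admits a methylation site to the models. The only data described are the OVCF patients and the natural-population controls. No part of the article mentions a hold-out set, cross-validation, optimism correction or an independent cohort.

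**The concern.** The two kinds of molecular predictor are treated differently. The genetic variants were chosen by other studies. The methylation sites are to be chosen here, from a genome-wide array, because they are associated with an outcome in these data. If the model is then fitted, its cut-off tuned and its accuracy scored in the same people, chance associations that helped a site to be chosen count again as predictive accuracy. Tuning t adds further optimism to sensitivity and specificity.

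The article promises accurate prediction models (end of Background) and motivates the work by the limited variance that genetic loci explain: 12% to 20% in the larger study that it cites. An in-sample R2 or AUC that includes in-study methylation sites is not comparable with such figures, and any comparison with the externally chosen variants is tilted towards methylation.

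**Working it through.** **1. The plan's own figure.** The only nearby number is the power statement under Sample size: "a sample of 500 cases and 500 controls would achieve 80% power to detect differential methylation at epigenome-wide significance" (P<1E-6) "with a methylation odds ratio of 1.28 or mean methylation differences of 5% in case–control designs of EWAS". No standard deviation is given, so the 80% cannot be reproduced directly. Solving for the SD, two-sided:

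- standardised difference = (4.892 + 0.842) × sqrt(2/500) = 0.363
- implied SD = 0.05 / 0.363 = 0.138

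Power would be 0.999 at SD 0.10, 0.65 at 0.15 and 0.17 at 0.20. This figure is not in dispute. It matters here because P<1E-6 is the only epigenome-wide threshold in the article, and it is not tied to choosing predictors.

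**2. How many null sites pass.** The number of sites after quality control is not stated. I assume 100,000 to 850,000, all independent.

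- Expected false sites at P<1E-6: 0.1 to 0.85.
- Chance that none passes: exp(−0.1) = 0.90 to exp(−0.85) = 0.43. At 700,000 sites it is exp(−0.7) = 0.50.
- Expected false sites at P<1E-5: 1 to 8.5.

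**3. One null site that only just passes.** Apparent AUC = Φ(4.892 × sqrt(1/n1 + 1/n0) / sqrt(2)).

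- 500 v 500: Φ(0.219) = 0.59
- 500 v 1000: Φ(0.189) = 0.575

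The second size is included because the analysis section gives "1000 natural population controls from the Chinese Academy of Sciences", whereas Sample size gives 500.

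**4. The whole procedure under a complete null.** I simulated normal sites unrelated to outcome, selected them by t-test, fitted ordinary logistic regression, set t at the maximum of sensitivity plus specificity, and scored the same people. Fresh people were then scored with the same model. There were 5 replicates at 100,000 sites and 2 at 850,000; a replicate with no site counts as AUC 0.50. Ranges run from 100,000 to 850,000 sites, 500 v 500.

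| Selection rule | Mean sites | In-sample AUC | In-sample sens + spec |
|---|---|---|---|
| P<1E-6 | 0.2 to 1 | 0.52 to 0.57 | – |
| P<1E-5 | 1.8 to 9 | 0.61 to 0.74 | 1.19 to 1.35 |
| Top 10 (hypothetical) | 10 | 0.72 to 0.75 | 1.34 to 1.38 |
| Top 20 (hypothetical) | 20 | 0.78 to 0.82 | 1.44 to 1.50 |
| Top 50 (hypothetical) | 50 | 0.89 to 0.93 | 1.63 to 1.71 |

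In fresh people AUC was 0.485 to 0.507 and sensitivity plus specificity 0.963 to 1.024, as they should be with no signal. The first row agrees with step 3: one replicate in five with a site gives 0.8 × 0.50 + 0.2 × 0.59 = 0.518.

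**5. BMD, n = 500, null.** In-sample R2 was 0.04 to 0.05 with the single best site, 0.26 to 0.31 with the top 10, 0.40 to 0.45 with 20 and 0.60 to 0.67 with 50. In fresh people it was at most 0.007.

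**6. If refracture is modelled.** The recurrence range cited in the Background gives 0.062 × 500 = 31 to 0.518 × 500 = 259 refractures. With 850,000 null sites, an illustrative 130 v 130 gave in-sample AUC 0.59 at P<1E-6, 0.86 at P<1E-5 and 0.97 with the top 20. At 31 v 31 it was 0.73 at P<1E-6 and 1.00 at P<1E-5. Fresh-sample AUC was 0.46 to 0.50.

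**The case against.** The strongest reply is that the article never says the same people are used throughout. In-study sites and an optimised t are both compatible with a train/test split or nested cross-validation, and a condensed article may leave such detail to a fuller document. The first part stands: same-participant scoring is an inference from one described dataset and the absence of any split. But the article does fix the source of the sites, the models, the metrics and the tuning of t. Carried out as written, those steps give in-sample accuracy.

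A reader might also infer that this plan would report an AUC near 0.9 from noise. The documents do not support that. No top-ranked list is prescribed; a top 50 out of 700,000 implies a cut-off near 7E-5, about 70 times looser than P<1E-6. At P<1E-6 with 500 v 500 the inflation is small, and about half the time no null site enters. With 1000 controls it would be smaller still.

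Nor can one say that a claim of added value from methylation would succeed regardless. The section defines no comparison with and without methylation, and where no site is selected there is nothing to add.

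Two further limits are fair. The prediction section covers BMD and OVCF risk; refracture prediction is only a general aim in the Background. And the contrast that supplies the sites is not fixed: if sites found by comparing refracture with no refracture entered the model of OVCF against healthy controls, the selection bias simulated here would not apply directly. In-sample coefficients and the tuned t would still be optimistic.

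**Conclusion.** The concern holds in a limited form. The plan does not separate discovery and tuning from evaluation, so as written its R2, AUC, sensitivity and specificity are apparent values with an upward bias. The genetic variants escape the selection part of that bias, although their coefficients are also fitted in-sample.

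The direction is secure; the size is conditional. For the OVCF model at 500 v 500 with no signal, it runs from slight (mean AUC 0.52 to 0.57 at P<1E-6) through material (0.61 to 0.74 at P<1E-5) to severe (0.72 to 0.93) under a list of the top 10 to 50 sites, which is hypothetical. A refracture model on fewer patients would fare worse at each rule.

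These figures rest on 100,000 to 850,000 independent sites, few replicates, and selection on the same contrast that is predicted. Correlated sites would lower them. An unseen protocol or analysis plan that specifies validation would answer the point; nothing in the article indicates one.

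**What to change.** In Biomarker identification and prediction analysis:

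- State the rule by which methylation sites enter each model and which contrast supplies them.
- Repeat site selection, model fitting and choice of t inside the training folds of a repeated nested cross-validation.
- Report only held-out R2, AUC, sensitivity and specificity.
- Report the held-out change from adding methylation to age, sex and the genetic variants.
- If a refracture model is built, leave-one-centre-out folds can be used, since those patients come from the five hospitals. They do not suit the OVCF model, whose healthy controls come from a separate cohort.

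No extra patients or assays are needed. The cost is computing time, revised wording and lower reported accuracy.

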The objective of this study is to investigate the genetic and epigenetic markers associated with osteoporosis and bone mineral density, and their impact on refracture risk among elderly patients. We aim to collect vertebral body blood and peripheral blood samples from 500 patients with OVCF who will undergo detailed clinical assessments, genome-wide genotype and methylation profiling at baseline. Following the surgical intervention, these patients will be followed up for 1 year to monitor refracture events, during which clinical and genome-wide methylation data will be collected again. These valuable data will enable us to identify genetic and epigenetic markers that can predict OVCF and refracture risk in the elderly and develop accurate prediction models.

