### Eligibility criteria

(1) Elderly patients aged ≥ 60 years who underwent vertebral augmentation for OVCF and experienced recurrent fractures after the initial surgery; (2) Elderly patients aged ≥ 60 years with bone mineral density T ≤ -2.5.

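### The OVCF-risk AUC contrasts already fractured patients with matched, non-osteoporotic controls, so it overstates BMD-related markers and does not measure risk; the promised refracture prediction has no model

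*Protocol article*

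**What the plan says.** The modelling plan is in the Protocol article, Biomarker identification and prediction analysis: "To predict BMD and OVCF risk, we will use multiple linear regression and multiple logistic regression models, respectively". The predictors follow: "We will include sex and age as predictors along with independent BMD-related genetic variants identified in previous studies and methylation sites identified in this study". A further score is then announced, with no outcome named for it: "Fracture risk score will also be evaluated based on age, gender, bone mineral density (BMD), previous fracture history, family history, and other risk factors". Accuracy is R² for BMD and "the area under the curve (AUC) for OVCF risk", and for the classification threshold, "t will be optimized to maximize the sum of sensitivity and specificity".

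The groups are defined elsewhere. Sample size takes 500 operated OVCF patients and "500 healthy controls matched for age, gender, and race from the CAS cohort who did not develop OVCF or osteoporosis". Eligibility criteria adds for patients, as a second item, "Elderly patients aged ≥ 60 years with bone mineral density T ≤ -2.5", without saying whether the two items are joint or alternative. The Background objective says the data will serve to "identify genetic and epigenetic markers that can predict OVCF and refracture risk in the elderly and develop accurate prediction models", after one year of follow-up for refracture.

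**The concern.** A model called OVCF risk should say how well people who will fracture can be told apart from those who will not, in the population where it would be used. Here the cases are sampled at surgery for a fracture they already have. The comparison group was chosen to have neither that fracture nor osteoporosis and was matched on two of the model's own predictors. An AUC and a cut-off from such a contrast reflect partly how the groups were chosen. The section on clinical implications nevertheless expects the results to help find people at high risk, so modest markers could be presented as clinically useful.

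The second issue is a mismatch between aim and analysis. Refracture is the fracture event that the cohort observes prospectively, and the objective promises its prediction, but the modelling section names no refracture model.

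**Working it through.** **Stated figures.** The article gives no AUC and no sample-size reasoning for a prediction model, so there is nothing to reproduce. Its 80% power for 500 v 500 concerns the EWAS and is not in question here.

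**Which contrast is possible.** Every recruited patient has an operated OVCF, including the in-cohort comparison group without refracture (Inclusion criteria for the control group). The only OVCF-free people are the CAS controls. A logistic model of OVCF must therefore contrast operated patients with those controls.

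**Age and sex.** AUC = P(case value ranks above control value) + ½ P(tie). Equal distributions give 0.50. Simulated check: 500 matched pairs, age assumed normal with mean 72 and SD 7, matched within 2 years, 500 repeats. Mean AUC was 0.500, 95% range 0.496 to 0.504.

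**BMD.** If all cases have T ≤ -2.5 and all controls T > -2.5, every case lies below every control and the AUC is 1.00. This needs no distributional assumption. If the two eligibility items are alternatives and a share q of cases has T > -2.5, then AUC = (1 − q) × 1 + q × A = 1 − q(1 − A), where A is the BMD AUC between those cases and the controls.

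**BMD-related markers.** The Background gives 5% and 12% to 20% of BMD variance explained by known loci. The remaining inputs are assumptions:

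- T-score normal, SD 1.2, mean μ of -1.0, -1.5 or -2.0.
- Logit of fracture = −2.2 − ln(2) × (T − μ)/1.2, so odds ratio 2 per SD lower BMD.
- Marker score = −√R² × (T − μ)/1.2 + √(1 − R²) × standard normal noise, so it acts on fracture only through BMD.
- 400,000 people per setting. Selected contrast: fracture with T ≤ -2.5 v no fracture with T > -2.5. Unselected contrast: fracture v no fracture.

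| Predictor | AUC, selected groups | AUC, unselected |
|---|---|---|
| Marker, R² 0% | 0.50 | 0.50 |
| Marker, R² 5% | 0.62 to 0.63 | 0.54 |
| Marker, R² 12% | 0.68 to 0.70 | 0.56 to 0.57 |
| Marker, R² 20% | 0.73 to 0.76 | 0.58 to 0.59 |
| BMD itself | 1.00 | 0.68 to 0.69 |

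Ranges run over the three values of μ. At μ = -1.5 and R² = 12% the pair is 0.688 v 0.566, an excess of 0.122. A threshold optimised on the selected groups depends on the same contrast.

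**Refracture.** The objective names prediction of OVCF and refracture. The modelling section names BMD (R²) and OVCF (AUC), and the abstract's multi-omics models name OVCF only. For refracture, the analysis section plans an EWAS and meQTL comparison with equal numbers of patients without refracture, plus methylation change over the year. These are association analyses; with controls selected in equal number, they do not by themselves give absolute risk. Events available in 500 patients at the Background's recurrence rates: 500 × 0.062 = 31 and 500 × 0.518 = 259. The article attaches no time horizon to those rates, so one-year counts may differ.

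**The case against.** A reader might infer that the OVCF model's AUC is fixed by design because its own predictors selected the groups. The text does not support that. BMD and previous fracture are named for the separate fracture risk score, not for the OVCF model, and that score has no stated outcome. The OVCF model's marker AUC runs from 0.50 to 0.76 in the table above: it is inflated, but it still depends on marker strength. Previous fracture separates the groups by definition only if the index OVCF counts as previous, which is not stated. The 1.00 for BMD needs the eligibility items to be joint. If they are not, the marker inflation would shrink too. Matching is stated for 500 controls but not for the 1000 mentioned elsewhere.

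A reader might also infer that refracture is ignored or is the only follow-up outcome. Neither holds: it gets the association analyses above, and bone metabolism, function score, SF-36 and methylation are measured again. Sampling after fracture may affect methylation but cannot alter germline variants. A full protocol or SAP might contain a refracture model.

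These points narrow the finding without removing it. The article itself names the modelled outcomes and metrics, and they do not match its objective. Whatever the fracture risk score is tested on, the OVCF AUC can come only from prevalent cases and selected controls.

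**Conclusion.** The concern holds in a limited form. The planned AUC and threshold describe how well prevalent, operated OVCF can be told from healthy, non-osteoporotic controls. They do not measure OVCF risk in unselected elderly people. With matching as stated, age and sex contribute about 0.50. BMD-related markers gain roughly 0.08 to 0.17 in AUC across R² of 5% to 20% (0.62 − 0.54 to 0.76 − 0.59), given the assumed T-score distribution, fracture odds ratio and joint eligibility items. A score containing BMD would separate the groups completely on the joint reading, and less so otherwise. Separately, the promised refracture prediction has no model in the modelling section. Whether refracture should be the main prediction target is the investigators' choice, and the documents do not require it.

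**What to change.** 1. First reconcile who is analysed. The Background objective and Sample size describe 500 OVCF patients followed for refracture. Eligibility criteria and the analysis section describe patients who have already refractured. The CAS controls number 500 in Sample size but 1000 in the analysis section and in Advanced features of this study. State also whether the two eligibility items are joint or alternative.
2. In the modelling section, call the OVCF v CAS result discrimination of prevalent OVCF from healthy non-osteoporotic controls. Report the gain from genetic and methylation markers conditional on age and sex. Report no AUC on these groups for any score that contains BMD or the index fracture, and state the outcome and sample for the fracture risk score.
3. Add a model of one-year refracture from baseline variables in the operated cohort, with the number of predictors limited by the events (31 to 259 at the Background's rates). At the low end only a very small model is feasible. Otherwise remove refracture prediction from the objective.

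The cost is wording and one extra model on data already to be collected, provided step 1 confirms that the cohort is followed for refracture. The OVCF AUC will carry a less favourable interpretation.

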## Background

Osteoporotic vertebral compression fractures (OVCF) are the most common fracture type in patients with osteoporosis, accounting for about half of osteoporosis-related fractures [1]. These fractures are associated with high morbidity and mortality [2], and vertebral augmentation is the standard operation for their treatment. While vertebral augmentation has significant effects in relieving pain and restoring vertebral height [3], it cannot fundamentally cure the fracture and prevent recurrence. Furthermore, the literature reports that the rate of recurrence of OVCF after vertebroplasty is high [4], ranging from 6.2% to 51.8% [5]. The debate on the risk factors of refracture after vertebral augmentation has lasted for nearly 20 years, but it is still inconclusive.

Osteoporosis is a complex disease caused by both genetic and environmental factors. While hundreds of genes and loci associated with osteoporotic fractures or bone mineral density have been identified through genome-wide association studies (GWAS), these can only explain a small proportion of the variation in the disease and its manifestations. For example, the 20 genes found in *GEFOS-1* explain only 5% of the phenotypic variation [6]. The hundreds of loci identified by the GWAS of bone mineral density based on UK biobank samples could only explain 12% to 20% of the phenotypic variation [7]. Therefore, the susceptibility genetic loci of osteoporosis found by GWAS alone cannot achieve accurate prediction of phenotypic changes, and even the prediction model based on a large number of genetic loci cannot achieve the accuracy required for practical applications in clinics.

Epigenetic modifications, including DNA methylation and histone modification, affect cell differentiation and development by affecting the structure and expression of genes, thereby regulating the genetic risk and environmental influence of various complex phenotypes and diseases [8]. Therefore, DNA methylation modification is considered as a bridge connecting genotypes and individual phenotypes. Epigenome-wide association studies (EWAS) of bone mineral density have discovered methylation sites playing a significant role in the pathogenesis of osteoporosis [9–15]. Furthermore, previous studies have revealed that exercise intervention for osteoporosis may achieve its effects by modulating the expression of bone metabolism genes via alterations in DNA methylation levels [16–18].

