### Clinical implications/impact of the study

The systematic analysis of molecular mechanisms underlying osteoporosis and bone mineral density phenotypes is of great importance, and this study aims to explore cross-omics molecular markers that affect these phenotypes based on multi-omics data and the degree of physiological aging. The research objectives of this study include:Conducting genome-wide association analysis and genome-wide epigenetic association analysis of osteoporosis and bone mineral density to identify genetic and epigenetic molecular markers related to these phenotypes and to deeply analyze their molecular mechanisms.Evaluating the feasibility of DNA methylation in assessing the effect of postoperative intervention for osteoporosis by analyzing changes in methylation levels of bone mineral density related sites in elderly patients with refracture after vertebral augmentation for OVCF within one year after surgery.Improving the risk prediction model of osteoporosis by considering multiple factors such as genetic variation and environmental factors, which can provide a scientific basis for the molecular classification and prevention of related diseases and serve as a paradigm for biomedical researchers conducting multi-omics life data research.

The results of this study can provide valuable insights into the molecular mechanisms of osteoporosis and bone mineral density phenotypes, which can facilitate the development of effective interventions and personalized treatments. The findings can also contribute to the establishment of a risk prediction model for osteoporosis that takes into account genetic and environmental factors, which can help identify individuals at high risk for developing osteoporosis and enable targeted preventive measures. Overall, this study has the potential to make significant contributions to the field of osteoporosis research and improve clinical practice in the management of related diseases.

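### Whole-model R2, AUC, sensitivity and specificity of one combined model cannot show whether methylation improves prediction over age, sex and published variants

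*Protocol article*

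**What the plan says.** All of the prediction analysis is in the Protocol article, section Biomarker identification and prediction analysis.

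- Models: "To predict BMD and OVCF risk, we will use multiple linear regression and multiple logistic regression models, respectively".
- Predictors: "We will include sex and age as predictors along with independent BMD-related genetic variants identified in previous studies and methylation sites identified in this study".
- Accuracy: "Prediction accuracy will be estimated using the R-squared correlation (R2) for BMD and the area under the curve (AUC) for OVCF risk".
- Further measures: "Sensitivities and specificities will be calculated using confusion matrices", at a threshold chosen to maximise their sum.
- A clinical fracture risk score is also to be evaluated, from age, gender, BMD, fracture history, family history and other factors. It is not named as a benchmark for the combined model.

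The aim appears elsewhere. The third objective under Clinical implications/impact of the study reads "Improving the risk prediction model of osteoporosis by considering multiple factors such as genetic variation and environmental factors", and Advanced features of this study repeats the intention. The Background gives the motive: loci from the large BMD study "could only explain 12% to 20% of the phenotypic variation", an earlier gene set explained 5%, and loci alone are judged too weak for clinical use. The Abstract promises multi-omics models that combine variants and methylation sites.

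**The concern.** The aim is comparative and the measures are absolute. A total R2 or AUC says how well everything in the model predicts together. It does not divide the credit between methylation, age, sex and variants that were already known. By the article's own account the known variants carry some predictive value, so a positive total is compatible with methylation contributing nothing. At stake is whether the methylation arrays improve prediction at all, which is the question that sets these models apart from existing genetic ones. The problem is not one of overfitting: it would remain if the combined model were validated perfectly in new people.

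**Working it through.** **Plan's own figure.** There is none to reproduce. The article gives no target R2, AUC or increment. The 80% power under Sample size concerns detecting single methylation sites, not prediction.

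**Inputs.** Variance explained by published variants: 5%, or 12% to 20% (Background). Assumed, because the article does not give them: age and sex explain 5% or 10% of BMD; 20 variants; 20 methylation sites unrelated to BMD; 5-fold cross-validation; N = 500 or 1000.

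**Step 1: held-out R2 of the combined model when methylation has no effect.** With training size m = 0.8N, p predictors and true explained share R, the expected held-out value is approximately

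1 − (1 − R) × [(m+1)/m] × [(m−2)/(m−p−2)].

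The combined model has p = 2 + 20 + 20 = 42; without methylation p = 22. The multiplier is:

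- m = 400: 401/400 × 398/356 = 1.121 (p = 42); 401/400 × 398/376 = 1.061 (p = 22)
- m = 800: 801/800 × 798/756 = 1.057 (p = 42); 801/800 × 798/776 = 1.030 (p = 22)

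| Age/sex + variants | N | Total R2, formula | Total R2, simulated | Gain from methylation, formula | Gain, simulated |
|---|---|---|---|---|---|
| 5% + 5% | 500 | 1 − 0.90×1.121 = −0.01 | −0.01 | −0.90×0.060 = −0.054 | −0.054 |
| 5% + 5% | 1000 | 1 − 0.90×1.057 = 0.05 | 0.05 | −0.90×0.027 = −0.024 | −0.024 |
| 10% + 12% | 500 | 1 − 0.78×1.121 = 0.13 | 0.12 | −0.78×0.060 = −0.047 | −0.048 |
| 10% + 12% | 1000 | 1 − 0.78×1.057 = 0.18 | 0.18 | −0.78×0.027 = −0.021 | −0.021 |
| 10% + 20% | 500 | 1 − 0.70×1.121 = 0.22 | 0.21 | −0.70×0.060 = −0.042 | −0.043 |
| 10% + 20% | 1000 | 1 − 0.70×1.057 = 0.26 | 0.26 | −0.70×0.027 = −0.019 | −0.019 |

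For sites not chosen on the outcome, the increment gives the right answer (no gain). The total is positive in every row except the first.

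**Step 2: AUC for OVCF.** If controls are matched on age and gender, as Sample size states, those two predictors add little and the variants carry the model. For a genetic score shifted by d standard deviations, AUC = Φ(d/√2). With d assumed at 0.3 to 0.6 this is Φ(0.21) = 0.58 to Φ(0.42) = 0.66. A cross-validated simulation of 500 cases and 500 controls, with variants assumed to explain 5% to 20% of liability, gave 0.59 to 0.71. The mean AUC gain from null methylation sites was −0.01 to −0.02.

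**Step 3: does a nested comparison suffice?** Not by itself. The plan's sites are "methylation sites identified in this study". With 20,000 independent noise probes and the top 20 chosen on the full sample before cross-validation, the R2 gain from methylation was falsely about +0.20 at N = 500 and +0.11 at N = 1000, positive in every run. With 50,000 probes it was +0.24 and +0.13. Choosing the sites inside the training folds made the gain negative, as it should be.

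**The case against.** The strongest reply is that this is a condensed article, and that a nested comparison is detail for an analysis plan that is not shown. In part this stands: the article does not say that no reduced model will be fitted, and a reader should not infer that one is ruled out. But the article does fix the model types, the predictors, the metrics and even the threshold rule. What it fixes does not match its comparative aim.

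Second, the third objective names genetic and environmental factors, not methylation. That is correct, and it would be wrong to say that this objective itself promises a methylation gain. The link comes from the Background and the Abstract, where methylation is what is added because loci alone predict too little.

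Third, the article already offers comparators: the fracture risk score, and the 12% to 20% in the Background. The score is not named as a comparator and uses different inputs, so a difference from it would not isolate methylation. The published percentage does not serve either: in the last row of the table the total is 0.26, above 20%, with no methylation effect.

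Fourth, the plan sets no significance test or success threshold for R2 or AUC. This stands in full. A reader might infer that the plan would declare success whatever methylation does; the article contains no such rule.

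**Conclusion.** The point holds in this form: the stated measures cannot show whether methylation adds to prediction, and a more informative method is available at little cost. With zero methylation effect, total held-out R2 for BMD is about 0.12 to 0.26 (age and sex assumed at 10%, variants at 12% to 20%), and AUC for OVCF is about 0.59 to 0.71 under the assumed liability shares.

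It would be too strong to say that the total always looks favourable. With 5% for age and sex and 5% for variants, held-out R2 is −0.01 at N = 500 and 0.05 at N = 1000. The masking is clearest for BMD; age and gender matching limits it for OVCF. The age/sex share, the liability shares and the numbers of variants and sites are assumptions. The mismatch between aim and measure does not depend on them; only its size does.

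**What to change.** In Biomarker identification and prediction analysis, specify three nested models on the same participants and the same folds:

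- (a) sex and age;
- (b) model a plus published BMD variants;
- (c) model b plus methylation sites, with site selection repeated inside each training fold or done in a separate discovery set.

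Report the held-out differences c minus b and b minus a (delta R2 for BMD, delta AUC for OVCF) with 95% confidence intervals. Base any statement that methylation improves prediction on c minus b, and keep total R2 and AUC as descriptive results.

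Add habit or clinical factors to model (a) only where every participant in that model has them. The Survey contents and methods section describes clinical data collection for OVCF patients, so the 34 habit items may not exist for the natural-population controls.

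Cost: a few sentences, two extra model fits per outcome, and site selection repeated within folds (or participants set aside for discovery). The headline becomes a smaller number whose interval may include zero.
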